## Trial setting

The EMS teams in Hsinchu County will be enrolled in the study once the necessary equipment, including the APV and Zoll X-series, is ready.

The EMT-P personnel are trained and authorized to perform endotracheal intubation (ETT) and supraglottic airway (SGA) insertion, while EMT-2 personnel are trained and authorized to perform SGA insertion. According to the regulations of the Taiwan Ministry of Health and Welfare, EMT-2 personnel must complete a minimum of 280 hours of training, while EMT-P personnel are required to complete 1,280 hours of training.

Hsinchu County is a rapidly growing area with a population of approximately 560,000 people. The county covers an area of 1,427 km² and is known for its significant contributions to Taiwan's technology sector. The population is predominantly Taiwanese, with a mix of Hakka, Han Chinese, and other ethnic groups.

The CONSORT flow diagram of this trial is illustrated in Figure 1.

Figure 1. CONSORT flow diagram of the trial

[figure not shown]

## Randomization and blinding

The participating EMS teams will be divided into two randomized clusters. Each cluster will be assigned to either the APV or BVM group. The duration of a cluster is 14 days (two weeks). The study center will instruct the clusters to alternate between APV and BVM according to a sequence determined by random allocation.

The randomization process was done by a research assistant. The sequence was generated using tool by Sealed Envelope Ltd. 2022 [20]. The formula this program used is based on the textbook *Clinical Trials: A Practical Approach* [21]. In the program, the seed is generated by a random table by Microsoft Excel. Each block contains 6 clusters. However, the EMTs are not aware of the randomization and allocation method.

The allocation sequence will be revealed until three days before the next cluster begins via social network application.

Blinding of the EMTs or hospital staff is not feasible because the ventilation equipment used in the study cannot be blinded

## Pre-trial training program

Before the trial begins, all EMS teams will participate in a 2-hour training program that covers the study protocol and procedures. Following this training, the EMS teams will undergo a 2-month pilot phase to ensure all members are fully familiar with the trial protocol. During the pilot phase, the EMS teams will execute the trial protocol; however, the data collected during this period will be used solely for training purposes and procedural adjustments. Any new teams joining the trial must complete the same training and pilot phase before participating.

## Exposure management

- - 1. Intervention group

The intervention group will receive APV for eligible patients, as determined by the selection criteria. The APV will be connected to the advanced airway (either SGA or ETT) in a standardized manner. The APV is set to deliver one breath every six seconds, with a tidal volume of 500-600 mL and a pressure limit of 60 mmHg. All other advanced cardiovascular life support (ACLS) procedures will follow the OHCA operation guidelines. If the APV malfunctions, the EMS team will switch to bag-valve-mask (BVM) ventilation.

- - 1. Control group

The control group will receive BVM ventilation for eligible patients, as determined by the selection criteria. The BVM will be connected to the advanced airway (either SGA or ETT) in the same manner as in the intervention group. The EMT will manually deliver a breath every six seconds.

- - 1. Advanced airway management

The decision to insert an SGA or perform ETT intubation depends on the level of the EMT attending the OHCA rescue. Only EMT-P personnel are authorized to perform ETT intubation. If an SGA is initially inserted, switching to ETT during the same dispatch is not permitted. If two attempts at ETT insertion fail, an SGA should be used instead.

## Outcome measurement

- - 1. Primary outcome

The primary outcome of the trial is any ROSC (defined as prehospital ROSC or ROSC achieved after in-hospital resuscitation).

- - 1. Secondary outcomes

The secondary outcomes include the following:

- Prehospital ROSC: ROSC before hospital arrival
- 24-hour survival
- Survival to discharge
- Neurological function on discharge
- Ventilation rate in prehospital resuscitation
- Tidal volume in prehospital resuscitation
- End-tidal CO2 level in prehospital resuscitation
- Chest compression fraction in prehospital resuscitation
- Intravenous catheter insertion in prehospital resuscitation
- Epinephrine injection in prehospital resuscitation
- Satisfaction of EMT in prehospital resuscitation (Appendix 2)

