Despite these advantages, most research on mechanical ventilation during CPR has focused on in-hospital settings. The use of automated pneumatic ventilators (APVs) in the prehospital environment remains underexplored. APVs are designed to deliver consistent ventilation with minimal manual intervention, potentially freeing up EMTs to perform other critical tasks during resuscitation. This could be particularly beneficial in prehospital settings where resources and personnel are often limited [9].

There is a significant knowledge gap regarding the effectiveness of APVs as a substitute for BVMs in prehospital OHCA management. Key concerns include whether APVs can deliver sufficient ventilation without causing high plateau pressures that may lead to barotrauma. Addressing this gap is crucial for developing evidence-based guidelines that can enhance prehospital care and improve patient outcomes. This study aims to evaluate the effectiveness of APVs compared to traditional BVMs in the prehospital resuscitation of OHCA patients.

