## Hypothesis

The hypothesis of the trial was formulated using the PICO framework (Population-Intervention-Comparison-Outcome). The study focused on non-traumatic out-of-hospital cardiac arrest (OHCA) patients in Hsinchu County (Population). It hypothesized that patients treated with advanced airway management and automated pneumatic ventilation (Intervention) would achieve a higher rate of return of spontaneous circulation (ROSC) (Outcome) compared to those who received bag-valve-mask ventilation (Comparison).

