## Objective

The primary objective of this trial is to evaluate the clinical effectiveness of the automated pneumatic ventilation (APV) method in prehospital resuscitation of out-of-hospital cardiac arrest (OHCA) compared to the bag-valve-mask (BVM) method. The primary outcome is any return of spontaneous circulation (ROSC).

The secondary objectives include:

1. Comparing the ventilation parameters between the APV and BVM methods.
2. Evaluating the overall resuscitation quality in the APV and BVM groups.
3. Comparing the satisfaction levels of emergency medical technicians between the APV and BVM groups.

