# Sample Size Estimation

In the original version of sample size calculation, we chose a secondary outcome (ventilation rate) to be the reference to calculate the sample size. Because we couldn’t find any studies with a similar trial design and primary outcome as our study. The original sample size was 260 patients. However, in August 2024, we identified some comparable studies to guide our calculations more precisely.

We chose the pilot study by Shin et al., which compared automatic mechanical ventilation (MV) with manual bag ventilation (BV) during CPR [19]. In that study, the primary outcome, any ROSC, was achieved in 56.7% of the MV group and 43.3% of the BV group—values closely aligning with our expected ROSC rates. Thus, we conducted an initial power analysis in G*Power 3.1 using the following parameters: Z test family, difference between two independent proportions, two-tailed test, proportions of 0.567 and 0.433, alpha of 0.05, power of 0.8, and equal allocation (1:1). This analysis suggested 218 patients per arm, totaling 436.

To account for the clustering effect due to randomization at the EMS team level, we included an intraclass correlation coefficient (ICC). Our EMS teams are expected to recruit 3 patients per cluster (over 14 days). Given the substantial variability in OHCA patient conditions, we assumed a low ICC of 0.06. The design effect was therefore calculated as 1+(3−1) ×0.06=1.12, adjusting our sample size to 488. Finally, with an estimated 5% dropout rate, the final required sample size was increased to 514 patients.

Figure 3. Sample size calculation by G*Power 3.1

[figure not shown]

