# Data Collection and Follow-up

Data will be collected in the REDCap database set up at National Taiwan University Hospital. The following variables will be gathered from the rescue reporting form: patient demographics (age and sex), pre-existing comorbidities (hypertension, diabetes mellitus, COPD, asthma, liver disease, kidney disease, heart disease, seizure, psychotic disorder, and cancer), arrest characteristics (witnessed arrest and bystander CPR), arrest location (household, workplace, public space, and nursing home), and EMT-performed procedures (oral/nasal airway, SGA, ETT, mechanical CPR, AED, defibrillation, IO/IV catheter, epinephrine injection, and normal saline infusion). Prehospital ROSC will also be reported on the form. These data will be collected on a weekly basis.

Other prognostic outcomes (any ROSC, 24-hour survival, survival to discharge, and neurological function at discharge) will be collected from the reports of the hospitals to which the patients are sent. Follow-up frequency for these outcomes will be one month.

Ventilation and chest compression feedback data will be exported from the Zoll X-series in .csv format. These files will be uploaded to the REDCap database on a weekly basis.

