# Dummy Tables

| Table 1. Baseline characteristics | | |
| --- | --- | --- |
|  | APV | BVM |
|  | (n=XXX) | (n=XXX) |
| Age, years (mean ± SD) | XX ± XX | XX ± XX |
| Males, n (%) | XX (XX.X%) | XX (XX.X%) |
| Pre-existing comorbidity |  |  |
| Diabetic mellitus, n (%) | XX (XX.X%) | XX (XX.X%) |
| Hypertension, n (%) | XX (XX.X%) | XX (XX.X%) |
| Cancer, n (%) | XX (XX.X%) | XX (XX.X%) |
| COPD, n (%) | XX (XX.X%) | XX (XX.X%) |
| Asthma, n (%) | XX (XX.X%) | XX (XX.X%) |
| Stroke, n (%) | XX (XX.X%) | XX (XX.X%) |
| Liver disease, n (%) | XX (XX.X%) | XX (XX.X%) |
| Kidney disease, n (%) | XX (XX.X%) | XX (XX.X%) |
| Heart disease, n (%) | XX (XX.X%) | XX (XX.X%) |
| Seizure, n (%) | XX (XX.X%) | XX (XX.X%) |
| Psychotic disorder, n (%) | XX (XX.X%) | XX (XX.X%) |
| Witnessed arrest, n (%) | XX (XX.X%) | XX (XX.X%) |
| Bystander CPR, n (%) | XX (XX.X%) | XX (XX.X%) |
| Arrest location |  |  |
| Household, n (%) | XX (XX.X%) | XX (XX.X%) |
| Working place, n (%) | XX (XX.X%) | XX (XX.X%) |
| Public space, n (%) | XX (XX.X%) | XX (XX.X%) |
| Nursing home, n (%) | XX (XX.X%) | XX (XX.X%) |
| Others, n (%) | XX (XX.X%) | XX (XX.X%) |
| Oral airway, n (%) | XX (XX.X%) | XX (XX.X%) |
| Nasal airway, n (%) | XX (XX.X%) | XX (XX.X%) |
| SGA, n (%) | XX (XX.X%) | XX (XX.X%) |
| ETT, n (%) | XX (XX.X%) | XX (XX.X%) |
| Mechanical CPR, n (%) | XX (XX.X%) | XX (XX.X%) |
| AED, n (%) | XX (XX.X%) | XX (XX.X%) |
| Defibrillation, n (%) | XX (XX.X%) | XX (XX.X%) |
| IO, n (%) | XX (XX.X%) | XX (XX.X%) |
| IV, n (%) | XX (XX.X%) | XX (XX.X%) |
| Epinephrine, n (%) | XX (XX.X%) | XX (XX.X%) |
| Normal saline, n (%) | XX (XX.X%) | XX (XX.X%) |

| Table 2. Ventilation parameters between patients in APV and BVM group | | |
| --- | --- | --- |
|  | APV | BVM |
|  | (n=XXX) | (n=XXX) |
| Ventilation rate, bpm (median ± IQR) | XX ± XX | XX ± XX |
| Tidal volume, mL (median ± IQR) | XX ± XX | XX ± XX |
| EtCO2, mmHg (median ± IQR) | XX ± XX | XX ± XX |

| Table 3. Outcome comparison between patients in APV and BVM group | | |
| --- | --- | --- |
|  | APV | BVM |
|  | (n=XXX) | (n=XXX) |
| Prehospital ROSC, n (%) | XX (XX.X%) | XX (XX.X%) |
| Any ROSC, n (%) | XX (XX.X%) | XX (XX.X%) |
| 24-hour survival, n (%) | XX (XX.X%) | XX (XX.X%) |
| Survival to hospital discharge, n (%) | XX (XX.X%) | XX (XX.X%) |
| Good neurological function after discharge, n (%) | XX (XX.X%) | XX (XX.X%) |

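### Prehospital epinephrine is compared as given or not given, so ROSC before the first dose counts as a missed dose and may pull the APV proportion down

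*Protocol*

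**What the plan says.** Under Outcome measurement, the Protocol lists "Epinephrine injection in prehospital resuscitation" among the secondary outcomes. It gives no time point and does not restrict the denominator to patients still in arrest.

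Data Collection and Follow-up takes the item from the rescue reporting form, within a list of procedures performed that ends "IO/IV catheter, epinephrine injection, and normal saline infusion". No time of injection is listed. Prehospital ROSC comes from the same form.

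In Dummy Tables the item appears as "Epinephrine, n" with a percentage. It stands in the baseline table (Table 1), not in the outcome table (Table 3). The Analytic Plan names Pearson's chi-square or Fisher's exact test for categorical variables.

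The objective that the item most plausibly serves is "Evaluating the overall resuscitation quality in the APV and BVM groups" (Objective). Backgrounds describes APV as "potentially freeing up EMTs to perform other critical tasks during resuscitation". The Hypothesis section expects more ROSC with APV.

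**The concern.** A yes/no record over the prehospital phase merges two kinds of patient without epinephrine: those still in arrest whom the crew did not treat, and those whose circulation returned before a dose was given. Only the first kind says anything about crew performance. The trial expects its intervention to change the frequency of ROSC, so the second kind may be more common under APV. The APV proportion would then be lowered by a benefit of the device.

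At stake is the reading of one process measure under the resuscitation-quality objective. A lower figure under APV could be taken as poorer care. A null figure could also hide a real gain in drug delivery.

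**Working it through.** **The plan's own figure.** Sample Size Estimation uses 0.567 against 0.433, two-sided alpha 0.05, power 0.8 and 1:1 allocation. With pooled variance and no continuity correction:

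n = [1.960 × √(2 × 0.5 × 0.5) + 0.842 × √(0.567 × 0.433 + 0.433 × 0.567)]² / 0.134² = 217.4, so 218 per arm and 436 in total.

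436 × 1.12 = 488.3 (stated 488), and 488 / 0.95 = 513.7, so 514. The figure reproduces and is not in dispute. The two ROSC rates serve below as planning values.

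**Model.** Let p be the any-ROSC rate in an arm (0.567 APV, 0.433 BVM, from the Protocol). Let s be the share of any-ROSC events that are prehospital and precede the first dose. Let e be the chance of receiving epinephrine if there is no such early ROSC, equal in both arms. The Protocol gives neither s nor e, so both are assumptions. The model also assumes that a patient with early ROSC then receives no epinephrine before hospital arrival.

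P(epinephrine recorded) = e × (1 − s × p)

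APV − BVM = −e × s × (0.567 − 0.433) = −e × s × 0.134

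| s | e = 0.5 | e = 0.7 | e = 0.9 |
|---|---|---|---|
| 5% | −0.3 | −0.5 | −0.6 |
| 10% | −0.7 | −0.9 | −1.2 |
| 20% | −1.3 | −1.9 | −2.4 |
| 100% (extreme) | −6.7 | −9.4 | −12.1 |

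Entries are percentage points. With equal crew performance the sign is negative for any s above zero.

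**How much better crew work cancels it.** The gain in e under APV that brings the difference back to zero is e × s × 0.134 / (1 − s × 0.567).

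- s = 10%: 0.0067 / 0.9433 to 0.01206 / 0.9433, that is 0.7 to 1.3 points.
- s = 20%: 0.0134 / 0.8866 to 0.02412 / 0.8866, that is 1.5 to 2.7 points.

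**Against sampling error.** At e = 0.7 and s = 20% the proportions are 62.1% and 63.9%. With 218 per arm and clustering ignored, the standard error is √[(0.621 × 0.379 + 0.639 × 0.361) / 218] = 4.6 points, against a bias of 1.9. The chance of a significant result in the negative direction is about 3 to 6% at s = 10% and 5 to 9% at s = 20%, compared with 2.5% when there is no bias.

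**The same check on the *neither* category.** Counting only early ROSC, the proportion with no epinephrine and no early ROSC is (1 − e) × (1 − s × p). Its APV − BVM difference is −(1 − e) × s × 0.134. At e = 0.7 this is −0.4 points (s = 10%) or −0.8 (s = 20%), against −0.9 and −1.9 for the crude proportion. The distortion is smaller than the crude one when e exceeds 0.5 and equal to it at e = 0.5. A lower *neither* figure flatters APV.

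**The case against.** **Only a narrow window counts.** The assigned ventilation is connected after the advanced airway is in place (Study procedures and workflow), so a dose given before that cannot be affected. The planned gain is in "any ROSC (defined as prehospital ROSC or ROSC achieved after in-hospital resuscitation", and in-hospital ROSC cannot change prehospital epinephrine. The Protocol gives neither a prehospital ROSC rate nor drug timing, and Appendix 1 with the local ACLS procedure is not shown. This stands and limits the size. It does not remove the problem. Patients who never receive an advanced airway are excluded, so many of those left with ROSC and no epinephrine may have had ROSC while the assigned ventilation was in use.

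**The premises are inferred.** The quality objective does not name epinephrine, no passage says that less epinephrine means worse care, and the yes/no scale comes from a data list and a baseline-table row. This stands as a caution, but the Protocol offers no other scale or purpose for the outcome.

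**This is SAP detail.** Denominators and competing events for a process measure are often left to the SAP, which is not at hand. That lowers the weight. However, the Protocol itself names the outcome, its data source, its tabulated form and the test, and together these fix the coding.

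**A stronger reading that does not hold.** A reader might infer that APV, if it works, will look like poorer resuscitation. The documents do not support this, because freed crew time pushes the proportion up and the balance is unknown. Larger figures also depend on the assumptions chosen. With e = 0.70 and ROSC before the first dose of 8% under BVM and 12 to 15% under APV, recorded epinephrine is 0.70 × 0.92 = 64.4% against 0.70 × 0.88 = 61.6% to 0.70 × 0.85 = 59.5%, a deficit of 2.8 to 4.9 points. That lets the early share of ROSC rise from 8 / 43.3 = 18.5% to between 12 / 56.7 = 21% and 15 / 56.7 = 26%. Holding it at 18.5% gives 10.5% under APV and a deficit of 0.70 × 2.5 = about 1.7 points.

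**Conclusion.** The point holds in a limited form. As collected, tabulated and tested, the epinephrine outcome cannot separate a missed dose from ROSC before the first dose. If APV raises early prehospital ROSC, the APV proportion may be biased downward as a measure of resuscitation quality.

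The bias is about 0.7 to 2.4 points if 10 to 20% of any-ROSC events precede the first dose and e lies between 0.5 and 0.9. Neither range comes from the Protocol. It would be large only if most ROSC came before the first dose. The net direction of the observed difference is uncertain, so the Protocol does not show that the quality objective will be answered with the wrong sign. The matter concerns one secondary process measure and leaves the primary outcome untouched.

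**What to change.** Report three exclusive categories per arm: epinephrine given; prehospital ROSC without epinephrine; neither. Both fields are already on the rescue form, so the cost is a sentence in the outcome definition and extra rows in a table. State that a lower epinephrine proportion alone will not be read as poorer quality.

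Show *neither* as a supporting figure and not as the sole quality measure. It is itself slightly biased towards the arm with more ROSC. It also cannot identify a missed dose followed by ROSC, which falls into the middle category.

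If the times of first dose and of ROSC are already recorded, analyse time to first epinephrine with ROSC as a competing event and report a cause-specific hazard ratio. Data Collection and Follow-up does not list these times, so their availability must be checked first. If they are absent, the three-category table is enough for a measure of this weight.

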## Study procedures and workflow

- - 1. Weekly Group Assignment Announcement

Every Friday evening, the group allocation results are announced via the study group's communication app. If assigned to the intervention group, the paramedics must ensure that the APV device is functioning properly and place it in the ambulance. If allocated to the control group, the device should be removed from the ambulance. The new round of group allocation will begin on Monday at 8 AM.

- - 1. OHCA rescue

When the dispatch center reports an OHCA case, an OHCA is identified on scene, or a patient experiences cardiac arrest during transportation to the hospital, the EMTs will confirm whether the case meets the inclusion criteria. The EMTs will then perform ACLS and determine which advanced airway (ETT or SGA) to use based on the situation at the scene.

The standard ACLS procedure in Hsin-chu county is provided in Appendix 1.

- - 1. Device Setup After Establishing Advanced Airway

After establishing the advanced airway (SGA or ETT), the following equipment should be connected under the following sequence:

Patient → Endotracheal tube or supraglottic airway → HEPA filter → AccuVent sensor → End-tidal CO2 sensor → Automatic ventilator → Oxygen tank (Figure 1).

- - 1. Data Entry After Rescue

After completing the rescue, upon returning to the fire department, the EMT should log the case data into an Excel form and upload the rescue reporting form. Additionally, they should complete the satisfaction questionnaire after every successful patient recruit.

These data are stored in a secure database.

- - 1. Data Export from Zoll X-series

A designated staff member will export the case’s ventilation and chest compression physiological data from the Zoll X-series monitor and then upload to a secured database.

Figure 2. Equipment connection for enrolled OHCA patients.

[figure not shown]

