# Analytic Plan

Statistical Package for the Social Sciences (version 26.0; IBM Corp., Armonk, NY, USA) will be used for the statistical analyses in this study. Intention to treat analysis will be adopted for comparing outcomes between interventions. Firstly, descriptive statistics of demographics (Table 1), ventilation parameters (Table 2), and outcomes (Table 3) among APV group and BVM group will be presented as number (percentage) for categorical variables and median (interquartile range) for continuous variables. Categorical variables will be compared using Pearson’s chi-square test or Fisher’s exact test, while continuous variables will be compared using Mann–Whitney U test. Secondly, multivariable logistic regression will be conducted to investigate the association of different ventilation interventions and patients’ outcomes, adjusting for potential confounders. Subgroup analysis, presented as a forest plot, will also be performed to investigate the impact of different interventions on outcomes in different subgroups. We will also compare the adjusted absolute difference between ventilation parameters measured in the APV and BVM group using the linear mixed-effects model (LMM). For the LMM, variables including demographics, prehospital information, resuscitation managements were included as fixed effects, whereas each patient will be modeled as a random effect. Two tail p-values <0.05 will be considered as statistically significant and will be corrected with Bonferroni correction in post-hoc analyses.

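### Crews who know the arm log cases after the prehospital result is known, and no independent case list would reveal an eligible arrest left unlogged

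*Protocol*

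**What the plan says.** - **Allocation is open and known in advance.** Protocol, Randomization and blinding: "Blinding of the EMTs or hospital staff is not feasible because the ventilation equipment used in the study cannot be blinded". Study procedures and workflow: "Every Friday evening, the group allocation results are announced", with the new allocation starting the following Monday morning. Every crew therefore knows its arm before any arrest in that period.
- **Crews judge eligibility at the start.** Study procedures and workflow, OHCA rescue: "the EMTs will confirm whether the case meets the inclusion criteria". Resuscitation and the choice of airway come after this step in the text.
- **Crews create the record at the end.** Same section, Data Entry After Rescue: "After completing the rescue, upon returning to the fire department, the EMT should log the case data into an Excel form". The rescue form is uploaded at the same point, and "they should complete the satisfaction questionnaire after every successful patient recruit".
- **Part of the outcome is on the crew's own form.** Data Collection and Follow-up: "Prehospital ROSC will also be reported on the form". Outcome measurement counts either prehospital ROSC or ROSC after in-hospital resuscitation as the primary outcome. The other prognostic outcomes, any ROSC included, come from hospital reports.
- **No consent step registers a patient.** Ethics states that consent is waived for all participants.
- **Checks.** Data Management provides double entry, range checks and logical checks. The DSMB section provides a six-monthly review of data completeness.
- **Analysis.** Analytic Plan: "Intention to treat analysis will be adopted for comparing outcomes between interventions".

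**The concern.** When allocation is open and patients are not individually registered beforehand, the list of analysed patients is itself exposed to bias. Here the person who writes the record knows the arm and the prehospital result. A failed resuscitation in one arm might be logged less reliably, whether through fatigue, discouragement, a device problem or a view that the case did not really count. That arm's ROSC rate would then be inflated.

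The stated safeguards do not reach this. Double entry, range checks and logical checks need a record to check. A completeness review with no external list cannot see an arrest that was never entered. Intention to treat keeps patients in their allocated arm only once they are in the dataset. The interim ROSC comparison described under Interim analysis and stopping criteria would presumably draw on the same data. A larger sample would not remove the bias.

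**Working it through.** **1. The plan's own figures.** Inputs from Sample Size Estimation: 0.567 against 0.433, two-sided alpha 0.05, power 0.80, 1:1. The two-proportion z formula with pooled variance gives 218 per arm, 436 in total. The design effect is 1 + (3 − 1) × 0.06 = 1.12, and 436 × 1.12 = 488.3, stated as 488. Then 488 / 0.95 = 513.7, stated as 514. The sample size reproduces. The planned effect is 56.7 − 43.3 = 13.4 points, with 488 / 2 = 244 evaluable patients per arm.

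**2. What a crew can select on.** At logging the crew is described as knowing prehospital ROSC, not what happens later in hospital. The model must therefore remove prehospital failures, some of whom go on to achieve ROSC in hospital and so count as successes.

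**3. Formula.** Let p be the true any-ROSC rate in both arms, s the share of it that is prehospital, q = s × p, and m the fraction of prehospital failures left unlogged in one arm, at random among them. Then

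observed rate = [p − m(p − q)] / [1 − m(1 − q)].

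p = 0.433 is the manual-ventilation rate used in the protocol's calculation. s and m are assumptions, because the protocol gives neither. The range is s = 1/3, 1/2, 2/3 and m = 5%, 10%, 20%.

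**4. Worked cases at m = 10%.**
- s = 1/3: q = 0.1443, so (0.433 − 0.0289) / (1 − 0.0856) = 0.4041 / 0.9144 = 0.4419, a shift of 0.89 points.
- s = 2/3: q = 0.2887, so (0.433 − 0.0144) / (1 − 0.0711) = 0.4186 / 0.9289 = 0.4506, a shift of 1.76 points.

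**5. Shift in the affected arm, in percentage points, with no true effect.**

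| m | s = 1/3 | s = 1/2 | s = 2/3 | limit, s = 1 |
| --- | --- | --- | --- | --- |
| 5% | 0.43 | 0.64 | 0.85 | 1.26 |
| 10% | 0.89 | 1.33 | 1.76 | 2.60 |
| 20% | 1.97 | 2.91 | 3.82 | 5.54 |

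The last column reduces to p / [1 − m(1 − p)]. It removes only patients who never had ROSC anywhere. That would require crews to know the in-hospital result as well, or all ROSC to be prehospital. It is an upper bound for a given m.

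**6. Patients involved.** Unlogged cases = 244 × m × (1 − q). At m = 10% this is 244 × 0.10 × 0.8557 = 20.9 for s = 1/3, and 244 × 0.10 × 0.7113 = 17.4 for s = 2/3.

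**7. Effect on the test.** Take m = 20% and s = 2/3. The affected arm has 244 × 0.8577 = 209.3 patients at 0.4712, against 244 at 0.433. The pooled rate is 0.4506, and the null standard error is √[0.4506 × 0.5494 × (1/209.3 + 1/244)] = 0.0469, so the critical difference is 1.96 × 0.0469 = 0.0919. The unpooled standard error is also 0.0469. The rejection probability is Φ[(0.0382 − 0.0919) / 0.0469] + Φ[(−0.0382 − 0.0919) / 0.0469] ≈ 0.126 + 0.003 = 0.13, against a nominal 0.05. The same steps at m = 10% and s = 2/3 give about 0.07. Clustering is ignored here.

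**The case against.** **Timing.** A reader might infer that crews decide eligibility after seeing the outcome. The protocol does not support this: the inclusion check comes before resuscitation. Only logging clearly follows the prehospital result. The advanced-airway exclusion is also settled late, but that is a separate matter.

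**Size.** A reader might take 1.3, 2.6 and 5.5 points as the likely bias. Those figures assume selection on the complete primary outcome. In-hospital ROSC comes from hospital reports and is not described as known to the crew at logging, so the smaller range applies. The omission rates are themselves illustrative.

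**Dead-on-arrival exclusion.** It may look like a second route for discarding failures. It is weak support: it lists obvious signs of death present on arrival, before any trial ventilation, and inclusion already requires attempted resuscitation. Nothing in the text makes it act differently by arm.

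**Other safeguards.** The DSMB does review completeness, a designated staff member exports monitor data, and hospitals supply outcomes. The CONSORT figure is not available in the text reviewed, so a screening step there cannot be ruled out. Nor does the protocol say outright that the Excel log defines the analysis set. These points count, but none is described as being used to find an arrest that the crew did not log.

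**Left to other documents.** One could call reconciliation a data-management detail. However, the protocol itself fixes who records cases and when, and case finding is trial conduct rather than something usually left to a SAP.

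**Conclusion.** The concern holds as a route to bias that the plan leaves open. It does not show that bias has occurred, or in which direction it would run. Crews who know the arm create the record with one component of the primary outcome in view, and no described check compares the records with an independent list.

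The size is modest at low omission rates. Up to 10% omission of prehospital failures in one arm shifts that arm by less than 2 points. At 20% the shift is 1.97 to 3.82 points, at most about 29% of the planned effect (3.82 / 13.4). These figures rest on a 43.3% any-ROSC rate in both arms, one-third to two-thirds of it prehospital, and omission confined to one arm and unrelated to later in-hospital ROSC. A change is worth making because the loss would be invisible and a larger sample would not remove it, while the remedy is inexpensive.

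**What to change.** In Study procedures and workflow, state that the trial population is every eligible arrest attended by a participating team during an allocated period, whether or not the crew logged it.

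Within the weekly collection already set out in Data Collection and Follow-up:
- Reconcile logged cases against dispatch records, ambulance run reports and monitor files. A dispatch list alone is not enough, because the protocol also admits arrests found on scene or occurring in transport.
- Retrieve missing rescue forms.
- Report unlogged cases and each exclusion by arm.
- Where existing staff allow, confirm exclusions without reference to arm or outcome. This needs some redaction, since the rescue form carries prehospital ROSC.

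The cost is some late queries to crews and modest data-management work, subject to access to dispatch records. The target of 514 does not change. This does not resolve the separate exclusion of patients in whom no advanced airway was placed, which still acts after allocation.
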